### Statistical analysis

Data will be analyzed according to the modified intention-to-treat (mITT) principle. Patients who have been randomized into the study and received at least one dose of ceftriaxone are included in the mITT analysis group. In the primary analysis, analysis of covariance (ANCOVA) will be used to compare the three study arms, with gender and the baseline value of the dependent variable as covariates. Pairwise comparisons are performed for the different treatment modalities with Bonferroni correction for multiple comparisons. Missing data will be imputed by carrying the last observation forward, in order to obtain a conservative estimate of the treatment effect. No interim efficacy analysis will be performed. Two-sided 5% significance levels will be used to identify statistically significant results. All confidence intervals reported will be 95% confidence intervals. All statistical analyses will be performed using SPSS software.

A sensitivity analysis will be performed on the per-protocol subgroup. The per-protocol population comprises of patients for whom all of the following apply: has met the in- and exclusion criteria; has taken at least 75% of the study drugs as recorded by MEMS; has not taken any other antimicrobial drug for more than 5 days during the study period; has not taken any prohibited concomitant medication; has not been unblinded before end of study.

When a difference between one of the experimental treatments (ceftriaxone followed by 12 weeks of either of the oral treatments) and the reference treatment (two weeks ceftriaxone followed by placebo) is found, subgroup analyses will be performed to identify factors that may affect the treatment outcome. This will be done by adding the factors and their interaction with the treatment to the analysis of covariance model. The duration of treatment effect will be evaluated in an explorative way with linear mixed models. When an outcome variable is measured more than once, a random (patient-dependent) intercept will be included in the analysis.

To evaluate the neuropsychological outcomes, results on individual tests will be standardized into z-scores to make across-test comparison possible (using baseline group mean and standard deviation as reference), and averaged into cognitive domain scores. Higher z-scores reflect a better performance. If necessary, scales will be inverted, e.g., in the case of reaction times where higher scores reflect a slower performance.

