### Randomization and blinding

After obtaining informed consent and completing the baseline assessment, patients are randomly assigned to one of three groups in a 1:1:1 allocation ratio (Figure 1). The randomization is computerized and balanced by minimization for age (<or ≥40 years), gender, duration of symptoms (<or ≥1 year), and baseline Global Health Composite score of the RAND-36 Health Status Inventory (RAND SF-36), consisting of all RAND SF-36 subscales [22]. The randomization list consists of consecutive medication numbers that are entered into a secured web-based database by an independent web manager. All personnel involved in the study (except the web manager and study pharmacist) and participants are masked to treatment allocation. If the code is broken, it renders the patient non-eligible. To assess success of masking, patients are asked at the week 14 evaluation whether they think they have received oral antibiotics or placebo.

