### Outcome measures

The primary outcome measure is health-related quality of life at EOT (week 14), assessed by the physical component summary score (PCS) of the RAND-36 Health Status Inventory (RAND SF-36) [22]. This score is based on the weighed subscale scores of the four physical RAND SF-36 subscales (physical functioning, role limitations due to physical health problems, pain, and general health perceptions). The PCS is transformed to norm-based T-scores (with a mean of 50 and a standard deviation of 10 in the general population) and ranges from 15 to 61, with higher scores indicating a better physical quality of life.

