### Sample size

The final power calculation was based on a pilot study on 80 patients with borreliosis-attributed persistent symptoms ([name] et al., unpublished). Patients were classified as having a poor or reasonable clinical condition as assessed during the first clinical consultation at the outpatient clinic. The difference in the PCS score between patients with a poor and those with a reasonable clinical condition was 3 points, with a standard deviation of 8. This corresponds with the minimally clinically important difference (MCID) of 2 to 5 points that has been proposed for the PCS [46]. In order to detect a difference of 3 points with a power of 90%, a two-sided alpha of 5% and a reliability coefficient (correlation between consecutive measurements) of 0.7 [47], a minimum of 75 patients are required per treatment group (225 patients in total). To compensate for possible loss to follow-up, a study population of at least 255 patients is targeted for.

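### The primary ANCOVA leaves out age and symptom duration, and covers the Global Health Composite only by proxy, although all three were minimisation factors; if they are prognostic, the test is mildly conservative

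*Protocol article*

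**What the plan says.** Under "Randomization and blinding", the protocol article describes computerised allocation to three equal groups, "balanced by minimization for age (<or ≥40 years), gender, duration of symptoms (<or ≥1 year), and baseline Global Health Composite score". It describes that composite as "consisting of all RAND SF-36 subscales".

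Under "Statistical analysis", the primary comparison of the three arms is an ANCOVA "with gender and the baseline value of the dependent variable as covariates". Pairwise comparisons follow with Bonferroni correction. No reason is given for keeping gender and dropping the other minimisation factors.

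Under "Outcome measures", the primary outcome is the RAND SF-36 PCS at week 14: "This score is based on the weighed subscale scores of the four physical RAND SF-36 subscales". For this outcome the baseline covariate is therefore baseline PCS.

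Under "Sample size", the calculation takes credit for one covariate only, through "a reliability coefficient (correlation between consecutive measurements) of 0.7".

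**The concern.** Minimisation forces the arms to be alike on the chosen factors, so those factors add little or nothing to the chance difference between arms. A model that leaves them out still counts their effect on the outcome as residual error. If they are prognostic, the model-based standard error describes a trial with less balance than this one has. Intervals are then wider than they should be, the test rejects less often than its nominal level, and some power is given away.

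A conservative error is not neutral here. The article expects the trial to inform both prescribing and withholding prolonged treatment, and an overstated standard error makes a null result slightly more likely and slightly less informative. The covariate set is stated explicitly, so this concerns what the article fixes and not a detail left to an unseen analysis plan.

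**Working it through.** **Inputs from the article ("Sample size").** Difference 3 points, SD 8, correlation 0.7, two-sided 5%, power 90%, 75 patients per arm.

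**Assumption.** Let q be the share of residual PCS variance (after baseline PCS) that age, symptom duration and the remainder of the composite explain. The article gives no value, so q is taken as 0, 0.02, 0.05 and 0.10. Gender, already in the model, is ignored in the arithmetic.

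**Step 1: reproduce the plan's figure.** Residual variance after baseline adjustment is 64 × (1 − 0.7²) = 32.64. Then n per arm = 2 × 32.64 × (1.960 + 1.282)² / 3² = 76.2, or 77, against the stated 75. Power at 75 per arm is 89.5%. Without baseline adjustment n would be 150, and with a change score 90. The plan's figure therefore rests on baseline adjustment alone and relies on none of the omitted factors.

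**Step 2: standard errors.** The model without the factors reports SE = √(2 × 32.64 / 75) = 0.933. If minimisation balances the factors, the true SE is 0.933 × √(1 − q). The overstatement is 1/√(1 − q).

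**Step 3: true size and power.**
- Size of a nominal 5% test without the factors: 2 × [1 − Φ(1.960 / √(1 − q))].
- Power with the factors left out: 1 − Φ((z × 0.933 − 3) / true SE).
- Power with the factors included: 1 − Φ(z − 3 / true SE).
- z = 1.960 for two-sided 5%; z = 2.394 for 5%/3, taking Bonferroni over all three pairwise comparisons.

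| q | True SE | SE overstated by | True size at nominal 5% | Power at 5%: omitted / included | Power at 5%/3: omitted / included |
|---|---|---|---|---|---|
| 0 | 0.933 | 0% | 5.0% | 89.5 / 89.5 | 79.4 / 79.4 |
| 0.02 | 0.924 | 1.0% | 4.8% | 89.8 / 90.1 | 79.7 / 80.4 |
| 0.05 | 0.909 | 2.6% | 4.4% | 90.1 / 91.0 | 80.0 / 81.7 |
| 0.10 | 0.885 | 5.4% | 3.9% | 90.7 / 92.4 | 80.7 / 84.0 |

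From unrounded values, the power forgone for q = 0.02, 0.05 and 0.10 is 0.4, 0.9 and 1.6 points at 5%, and 0.7, 1.7 and 3.4 points at 5%/3.

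**Step 4: patient equivalents.** These come from solving for the n at which the model without the factors reaches the power of the model with them at 75 per arm. The extra patients per arm are 0.9, 2.3 and 4.8 at 5%, and 1.1, 2.9 and 5.8 at 5%/3. The simpler figure 75 × q (1.5, 3.75, 7.5) is too high, because it treats the estimate itself as noisier, which Step 5 shows it is not.

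**Step 5: simulation check.** Three-arm minimisation was simulated with 225 patients and 3,000 runs per setting. It assumed a probability of 0.8 for the preferred arm and a correlation of 0.85 between the composite and baseline PCS.
- Omitted factors not prognostic: mean model SE 0.935 for the protocol model and 0.936 with the factors added.
- q about 0.03: mean SE 0.934 against 0.920; power at 5% was 90.0% against 90.4%.
- q about 0.13, beyond the range above: mean SE 0.934 against 0.875; type I error 3.8% against 4.7%; power at 5% 90.6% against 92.9%. The empirical SD of the estimate was 0.872 against 0.869.

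The estimate is almost equally precise either way. What the protocol model gets wrong is the reported standard error.

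**The case against.** The case for leaving the model alone has several sound parts.

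- **Overlap.** A reader might infer that three of the four minimisation factors go unadjusted. For the PCS that goes too far. The composite contains the four physical subscales that make up the PCS, so baseline PCS carries part of it. Only age and symptom duration are wholly absent. The overlap is incomplete, since the composite also includes the mental subscales, and baseline fatigue or cognition would be a weaker stand-in for it.
- **Conditional harm.** A reader might also infer that the standard errors are too large as a matter of fact. The article gives no prognostic strength for these factors beyond baseline and gender, and at q = 0 nothing is lost.
- **No stated property fails.** The sample size reproduces without these factors, the treatment estimate is unbiased and the error is on the conservative side.
- **Choice of alpha.** The larger power losses apply at the Bonferroni threshold, whereas the sample size uses 5%. Both are relevant: the article plans at 5% but tests pairs with Bonferroni correction. The figures should be shown side by side and not mixed.
- **Cognition.** It is tempting to say that the loss is larger for cognitive outcomes because age matters more there. No figure in the article supports this, and adjusting for baseline cognition already absorbs part of any stable age effect.

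These points limit the size of the concern. They do not remove the unexplained mismatch between allocation and analysis.

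**Conclusion.** The mismatch is certain; its effect is conditional and small. If age, symptom duration and the part of the composite not captured by baseline PCS explain up to 10% of residual variance, the standard error is overstated by at most about 5% and the true size of a nominal 5% test falls no lower than 3.9%. The power forgone is at most 1.6 points at 5% or 3.4 points at 5%/3, worth at most about 5 or 6 patients per arm respectively.

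These figures rest on the assumed range for q, close balance from the minimisation, 75 analysed patients per arm and, for the second set, Bonferroni over three comparisons. The article does not support a claim of bias, inflated type I error, a materially noisier estimate or a failed sample-size basis. This is an inexpensive improvement to the analysis, not a flaw that threatens the trial's conclusion.

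**What to change.** Before unblinding, state that the primary and secondary ANCOVA models include age, symptom duration and baseline Global Health Composite, beside gender and the outcome's own baseline. Use each factor in the form applied in the minimisation, or as a continuous variable. The article gives no cut-point for the composite, so the plan must state the one used or enter the composite as continuous. If the sponsor prefers the shorter model, it should give the reason.

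The overlap between the composite and baseline PCS does not harm the treatment estimate, because both are measured before allocation. The cost is one sentence and about three degrees of freedom: with 225 patients and five parameters in the current model, 220 become 217. No new data are needed, and if the factors are not prognostic, essentially nothing is lost.

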### Assessments

An extensive baseline assessment is performed including questionnaires, measurement of physical activity, and clinical, laboratory, microbiological, and neuropsychological evaluation. Neurological symptoms are assessed by the lead study physicians using a standardized interview and clinical neurological examination at baseline and week 14 [25].

Study visits for safety evaluation are performed at week 2, week 8, and week 14 after baseline. Safety assessments include a medical history, physical examination, and laboratory investigation (hemoglobin, hematocrit, leukocytes, platelets, glucose, creatinin, alkaline phosphatase, alanine aminotransferase).

Efficacy evaluation is performed at week 14 (end of treatment period, EOT), week 26 (12 weeks after EOT), and week 40 after baseline (end of study, EOS, 26 weeks after EOT). After the last comprehensive outcome assessment at week 40, patients are surveyed by post-study questionnaires at week 52.

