To provide a standard treatment for all patients, and to cover potentially undiagnosed neuroborreliosis, all randomized patients receive an open-label course of i.v. ceftriaxone for 2 weeks preceding randomized blinded study drugs. In this respect, the present study differs from previous trials comparing prolonged therapy to placebo [10],[17],[18],[29]. By applying a standardized open-label treatment to patients in all treatment arms, the study is designed to compare short-term standard treatment [15] to prolonged therapy as advocated by several position papers [16],[53]. In addition, this approach does not leave potentially active infection untreated in patients who are randomized to the control arm, and it also controls for the wide variation in prior antibiotic therapies (or lack thereof) that patients with borreliosis-attributed persistent symptoms may have received.

As the primary outcome measure, we have chosen the physical component summary score (PCS) of the RAND-36 Health Status Inventory (RAND SF-36) [22]. The RAND SF-36 is similar to the Medical Outcomes Study (MOS) 36-item Short-Form General Health Survey (SF-36) [54]. The PCS, also known as the physical health composite score (PHC) [22], is computed by a non-orthogonal scoring algorithm. Several previous studies have used the alternate (SF-36) version of the PCS, applying a principal components analysis with orthogonal factors, with mental health components contributing negatively to this PCS score [54]. This SF-36 PCS has proven difficult to interpret as the level of mental health influences the physical health score and is therefore not purely a reflection of physical health. Furthermore, the SF-36 PCS is less sensitive to change than the underlying scales, while the RAND SF-36 PCS has been shown to be sensitive to change [55]-[62]. Despite the differences in calculation of both composite scores, they do correlate highly, indicating that they do represent similar constructs [58],[59].

In conclusion, the PLEASE study is expected to provide evidence for prescribing or withholding prolonged antibiotic treatment as compared to standard short-term treatment in patients with borreliosis-attributed persistent symptoms. In addition, this study may help to define subgroups of patients who may or may not benefit from additional antibiotic treatment, and contribute to a more cost-effective management of this disease entity.

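### Last observation carried forward is called conservative, but at week 14 it restores the pre-treatment baseline and can bias the primary contrast in either direction

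*Protocol article*

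**What the plan says.** All citations are to the protocol article.

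- Statistical analysis sets the missing-data rule and its reason: "Missing data will be imputed by carrying the last observation forward, in order to obtain a conservative estimate of the treatment effect". The rule is not limited to particular visits or outcomes. The analysis set is everyone randomised who had at least one ceftriaxone dose. The primary model is ANCOVA with gender and the baseline value, followed by Bonferroni-corrected pairwise comparisons.
- Outcome measures fixes the endpoint: "The primary outcome measure is health-related quality of life at EOT (week 14), assessed by the physical component summary score (PCS").
- Assessments gives the efficacy schedule: "Efficacy evaluation is performed at week 14 (end of treatment period, EOT), week 26 (12 weeks after EOT), and week 40 after baseline". It describes the earlier visits differently: "Study visits for safety evaluation are performed at week 2, week 8, and week 14 after baseline", and "Safety assessments include a medical history, physical examination, and laboratory investigation". No questionnaire is listed for weeks 2 or 8.
- Randomization and blinding places baseline before allocation: "After obtaining informed consent and completing the baseline assessment, patients are randomly assigned to one of three groups in a 1:1:1 allocation ratio". Intervention then gives every arm 14 days of open-label ceftriaxone before the blinded capsules.

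**The concern.** On this schedule, the only PCS available to carry forward to week 14 is the baseline score. Every patient with a missing primary outcome is treated as having changed by exactly zero, and any change that follows ceftriaxone in all arms is erased for that patient.

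This pulls the estimate towards zero only under certain dropout patterns. If all arms change and one arm loses more patients than the other, the erased common change no longer cancels between arms and appears as a treatment difference. Neither condition is far-fetched here: all arms start with the same open-label active drug, and the blinded regimens range from two active drugs to double placebo. The article fixes both the method and a property the method does not reliably have, so this is not a detail left to an unseen analysis plan. The primary estimate and its error rate are at stake.

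**Working it through.** **Inputs from the article (Sample size).** Difference 3 points, SD 8, correlation 0.7, two-sided 5%, power 90%, 75 per group, 255 enrolled in total (85 per arm).

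**Inputs that are assumptions.** Missing fractions by arm, mean placebo change Dc, and missingness unrelated to outcome within arm. The article gives none of these. The total missingness of about 12% matches its own allowance: (255 − 225)/255 = 30/255 = 11.8%.

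**1. The plan's own figure.** The ANCOVA residual SD is 8·√(1 − 0.7²) = 5.713. Then n = 2·(1.960 + 1.282)²·5.713²/3² = 76.2, rounded up to 77 per group. Power at 75 per group is 89.5%, so the stated 75 is reproduced to within two patients and these inputs describe the intended analysis.

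**2. Expected contrast with baseline carried forward.** Mean change is (1 − dT)(Dc + δ) on active and (1 − dC)Dc on placebo. The difference is

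δ(1 − dT) + Dc(dC − dT).

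The first term shrinks a real effect. The second can have either sign and vanishes only if dropout is equal or Dc is zero.

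**3. Numbers.**

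| True effect | Missing active / placebo | Dc | Expected contrast |
|---|---|---|---|
| 3 | 11.8% / 11.8% | any | 3 × 0.882 = 2.65 |
| 3 | 18% / 6% | 4 | 2.46 − 0.48 = 1.98 |
| 3 | 6% / 18% | 4 | 2.82 + 0.48 = 3.30 |
| 0 | 6% / 18% | 4 | 4 × 0.12 = +0.48 |
| 0 | 10% / 14% | 4 | 4 × 0.04 = +0.16 |

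A three-arm simulation with 85 per arm agrees: 1.98, 3.29 and +0.47 for the second to fourth rows, and +0.16 for the last.

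**4. False positives at the planned threshold.** Three pairwise comparisons under Bonferroni give 0.05/3 = 1.7% each (critical value 2.394). With no true effect, 6%/18% missing and Dc = 4, the simulated rejection rate per comparison is 3.8%. Without the correction (critical value 1.96) it is 9.2%. The chance that at least one active arm is falsely declared different from placebo is 6.8%, against a Bonferroni bound of 2 × 1.67% = 3.3% for those two comparisons. With 10%/14% missing, the per-comparison rate is 1.9%, essentially nominal.

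**5. Power for a true 3 points, 85 per arm, Bonferroni threshold.**

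| Missing active / placebo | Dc | Carried forward | Observed cases only |
|---|---|---|---|
| 12% / 12% | 0 | 77.8% | 79.5% |
| 12% / 12% | 4 | 71.8% | about 79% |
| 18% / 6% | 4 | about 43% | about 78–79% |

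Carried-forward baselines also reduce the residual variance and keep all 85 patients per arm, which is why the loss is small when Dc = 0. At the unadjusted 5% level with 11.8% missing and Dc = 0, power is 88.4% against 89.5%.

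**The case against.** The main objection is that the trial asks a superiority question, and for superiority, shrinkage towards zero is the ordinary meaning of conservative. With balanced dropout the method shrinks a real effect and creates no bias when there is none. Material inflation needs both a marked dropout imbalance and a sizeable common change, and the article gives neither. All of this stands. It limits the size of the problem, but it does not make the stated property true: whether dropout will be balanced is unknown in advance.

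The article also does not expressly rule out a PCS at weeks 2 or 8, and its flowchart is not available here. If one was taken, the carried value would follow at least part of the ceftriaxone course. The listed visit contents do not suggest this.

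Several stronger readings are tempting but not supported:

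- *The method always costs power.* It does not. The loss is 1 to 2 points with balanced dropout and no common change, and power rises when the bias favours active treatment.
- *False positives run at about 10%.* That figure belongs to an unadjusted 5% test, not to the Bonferroni comparisons planned.
- *Enrolling 255 gives no protection.* With 12% balanced missing and Dc = 4, power is 65.6% at 75 enrolled per arm and 71.8% at 85, so part of the loss is recovered.
- *The later analysis is biased towards a lasting effect.* The article says "The duration of treatment effect will be evaluated in an explorative way with linear mixed models", but not that carried-forward values enter those models, which can use incomplete data as they stand.
- *No missing-data sensitivity analysis exists.* The article names a per-protocol analysis, but a missing-data analysis may sit in the analysis plan, which is not shown.
- *Bias towards zero is itself unsafe because the trial may support withholding treatment.* The Discussion does say it is "expected to provide evidence for prescribing or withholding prolonged antibiotic treatment", but this is a secondary argument beside the superiority aim.

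**Conclusion.** The point holds in a limited form. On the listed schedule the imputation rule amounts to carrying baseline forward at the primary time point, and the claim that it gives a conservative estimate is not generally true. With balanced missingness near the planned 12%, a true 3 points is reported as about 2.65. With a three-fold imbalance and an assumed common improvement of 4 points, it becomes about 2.0 or about 3.3, depending on which arm loses more patients. With no true effect and more loss on placebo, the bias is about +0.5 and rejection per comparison is about 4% instead of 1.7%. With a mild imbalance, the bias is about 0.16 and inflation is negligible.

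Power loss is conditional: 1 to 2 points with balanced dropout and no common change, about 7 points with a common change of 4, and more when the active arm loses more patients. The direction and size in the actual trial cannot be known from the article, because they depend on dropout by arm and on the common change.

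**What to change.** Delete the statement that the imputation is conservative, and replace carrying forward in the primary analysis with a method valid under missing at random. Two options fit the existing design:

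- a likelihood-based mixed model for PCS at weeks 14, 26 and 40, with arm by visit, baseline PCS and gender, taking the week-14 contrast as primary; or
- the planned ANCOVA after multiple imputation that uses baseline and the later visits.

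In either case, use the observed week-14 PCS of patients who stopped study drug. Keep baseline-carried-forward or return-to-baseline imputation as a sensitivity analysis only, labelled as such.

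The cost is a change of analysis text and somewhat more analysis work. No data collection or sample size changes, and linear mixed models are already planned for another purpose. The gain has a limit: patients with no score after baseline add little under either option, and if most missing patients are of that kind the result will be close to ANCOVA on observed cases.

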### Concomitant medication

Any antibacterial drugs other than study medications are prohibited during the entire study period. In case of proven intercurrent infections (e.g., urinary tract infection), specific antimicrobial therapy may be given for a maximum of 5 days. Indications should be discussed with the investigator, and efforts should be made to select an antimicrobial drug with no *in vitro* activity against *B. burgdorferi*. The following drugs are prohibited because of potential interaction with study drugs or potential effects on efficacy of treatment: cisapride, astemizole, terfenadine, barbiturates, phenytoin, carbamazepine, prednisone, recombinant cytokines, hematopoietic growth factors, or immunoglobulins. If treatment with one of these drugs is required, the patient will be classified as therapy discontinuation.

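### The one per-protocol definition lets unblinding, and on the natural reading other antimicrobial use, up to week 40 remove patients from the week-14 sensitivity analysis

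*Protocol article*

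**What the plan says.** Outcome measures fixes the time point: "The primary outcome measure is health-related quality of life at EOT (week 14"). Assessments adds efficacy visits at weeks 26 and 40, labels the last one "week 40 after baseline (end of study, EOS, 26 weeks after EOT"), and says that afterwards "patients are surveyed by post-study questionnaires at week 52". By the article's own labels, the study therefore ends at week 40.

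Statistical analysis makes mITT the primary analysis and names one sensitivity analysis, on a per-protocol subgroup defined once. Apart from eligibility, that definition has four criteria:

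- Intake: MEMS must show that three quarters or more of the study medication was used.
- Other antimicrobials: the patient "has not taken any other antimicrobial drug for more than 5 days during the study period".
- Banned co-medication: none may have been used, and no time limit is attached to this.
- Treatment code: the patient "has not been unblinded before end of study".

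Concomitant medication sets the background rule: "Any antibacterial drugs other than study medications are prohibited during the entire study period".

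**The concern.** A per-protocol set is meant to keep patients who followed the protocol up to the point where the outcome was measured. Here a patient could take all study capsules, complete the week-14 PCS without any deviation, and still be removed from the week-14 analysis because of a code break or an antibiotic course at, say, week 30. That event cannot have influenced the week-14 score, so removing the patient does not serve the purpose of the set.

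The event may, however, depend on the score. The trial enrols people with persistent symptoms, and the article says that prolonged antibiotics are advocated in several position papers. Patients who feel no better at week 14 may be more likely to take further antibiotics or to have their allocation revealed. The set would then be selected on a consequence of the outcome, and a gap between the mITT and per-protocol results could no longer be read as showing the role of adherence.

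**Working it through.** **Step 1: how far each criterion reaches.**

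| Per-protocol criterion | Window in the article | Reaches past week 14? |
|---|---|---|
| Eligibility | At entry | No |
| At least 75% of study drug (MEMS) | Oral treatment, which ends at week 14 | No |
| Other antimicrobials, more than 5 days | The study period, not defined in words | Yes, on the natural reading |
| Prohibited medication | None given | Open |
| Unblinding | To end of study | Yes, explicitly |

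Two passages support the natural reading for antimicrobials. Concomitant medication applies its ban to the entire study period, and exclusion criterion 12 in Table 1 uses a different term for the therapy phase. The overhang is 40 − 14 = 26 weeks.

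**Step 2: inputs for the size.** Sample size gives a difference of 3 points, SD 8 and correlation 0.7. After baseline adjustment the residual SD is 8·√(1 − 0.7²) = 5.71. As a check on these inputs, 2·[5.71·(1.960 + 1.282)/3]² = 76.2 per group, close to the planned 75. The article gives no rate of later antibiotic use or unblinding and no relation to PCS, so both are assumptions below.

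**Step 3: difference in raw means.** Let week-14 PCS be normal with SD 8 and means 0 (placebo) and 3 (active). Let the chance of exclusion after week 14 be 1/(1 + exp[−(a − k·y/8)]), with the same a and k in both arms. The odds of exclusion then rise by exp(k) per 8 points lower PCS; k = 0.69, 1 and 1.5 give 2, 2.7 and 4.5. I set a to reach a given placebo exclusion rate and took the difference between the means of retained patients by numerical integration.

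| Placebo patients excluded | Odds 2 per SD | Odds 2.7 | Odds 4.5 |
|---|---|---|---|
| 2% | 2.98 | 2.95 | 2.91 |
| 5% | 2.94 | 2.90 | 2.82 |
| 10% | 2.90 | 2.81 | 2.69 |
| 20% | 2.82 | 2.69 | 2.50 |
| 30% | 2.77 | 2.60 | 2.37 |

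The loss runs from (3 − 2.90)/3 = 3% to (3 − 2.37)/3 = 21% at 10% to 30% exclusion, and from about 1% to 6% at 2% to 5%.

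**Step 4: the planned type of model.** I simulated 1,000,000 patients in two arms and fitted ANCOVA on baseline. Exclusion odds were 2 to 4 times higher per residual SD (5.71 points) of worse result. Exclusion rates here are over both arms together.

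| Setting | 10% excluded | 20% | 30% |
|---|---|---|---|
| True effect 3, same mechanism in both arms | 2.91 to 2.67 | 2.83 to 2.49 | 2.76 to 2.38 |
| True effect 3, placebo odds also doubled | 2.70 to 2.41 | 2.44 to 2.04 | 2.30 to 1.79 |
| No true effect, placebo odds doubled | −0.21 to −0.29 | −0.36 to −0.46 | −0.47 to −0.59 |

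With no true effect and the same mechanism in both arms, estimates stayed within 0.03 of zero. When exclusion was unrelated to the outcome, the 3-point effect came back (about 3.00 to 3.02), even with unequal exclusion rates.

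Bias therefore needs exclusion that depends on the outcome, together with either a true effect or unequal exclusion between arms.

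**The case against.** The best defence is that the article describes one trial-wide set and not a set made for week 14. Efficacy is assessed at weeks 14, 26 and 40, other antibacterials are banned throughout, and a set recording adherence to that ban is coherent. Separate windows per endpoint could be left to the full protocol or analysis plan. This does not dispose of the point: the article states the criteria itself, with windows, and nothing in it closes them at week 14 for the week-14 analysis. It is a rule fixed badly, not a detail left out. A definition elsewhere that ended the study period at week 14 would remove the antimicrobial part, but not the unblinding part.

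The defence is stronger on consequences, and the following stands:

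- Nothing in the article says that later antibiotic use or unblinding depends on PCS. Patients and staff are masked, no unblinding at a patient's request is described, and other antibacterials are allowed only for proven intercurrent infection and for at most 5 days. Later events may be rare.
- In the same-mechanism settings the loss is at most about 0.6 points, below the standard error of a pairwise comparison, 5.71·√(2/75) = 0.93. That limits its practical weight. It does not make the bias vanish, because mITT and per-protocol estimates share most patients and are read against each other.
- The primary analysis is mITT.

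**Conclusion.** The point holds as a defect in the definition of a sensitivity set. It is explicit for unblinding, follows from the natural reading for other antimicrobials, and is open for prohibited medication. Under the assumed odds the per-protocol difference falls from 3 to about 2.9 to 2.7 at 10% placebo exclusion, 2.8 to 2.5 at 20% and 2.8 to 2.4 at 30%, and is nearly unchanged at 2%. Larger distortion needs a further assumption, that exclusion is more frequent in one arm at the same outcome. These sizes rest on assumed rates and odds.

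A reader might infer more than the documents support:

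- *That every per-protocol rule runs to week 40.* Eligibility and study-drug intake do not.
- *That the outcome causes the later exclusions.* This is plausible in this population but not stated.
- *That the sensitivity analysis is necessarily biased or useless.* With no true effect and one mechanism in all arms there is no bias, and in the same-mechanism settings at least 79% of the effect is retained.
- *That the main result is at risk.* The mITT primary analysis and the sample size do not depend on this rule.

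**What to change.** Tie the windows to the visit being analysed. For the week-14 per-protocol analysis, count other antimicrobial use, prohibited medication and unblinding only up to the week-14 assessment. For any per-protocol analysis at week 26 or week 40, count them up to that visit. Give the prohibited-medication criterion an explicit window at the same time. Eligibility and study-drug intake need no change.

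This costs a sentence in the definition, ideally settled before unblinding, with no change to sample size, treatment or conduct. The one practical requirement is that the dates of these events are available. The article does not say that they are recorded, so this should be confirmed.
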